## Abstract

**Background:**

Microvascular angina (MVA) is a frequent condition for which our understanding of the disease pathophysiology and therapeutic perspectives remain unsatisfactory. The current study is designed to test whether an improvement in microvascular resistances could be achieved by elevating backward pressure in the coronary venous system, based on the hypothesis that an increase in hydrostatic pressure could cause a dilatation of the myocardial arterioles, resulting in a reduction of vascular resistances. This approach might have potential clinical implications, as it might suggest that interventions aimed at increasing coronary sinus (CS) pressure might result in a decrease in angina in this subset of patients. The aim of our single-center, sham-controlled, crossover randomized trial is to investigate the effect of an acute increase in CS pressure on a number of parameters of coronary physiology, including parameters of coronary microvascular resistance and conductance.

**Methods and analysis:**

A total of 20 consecutive patients with angina pectoris and coronary microvascular dysfunction (CMD) will be enrolled in the study. Hemodynamic parameters including aortic and distal coronary pressure, CS and right atrial pressure, and the coronary microvascular resistance index will be measured at rest and during hyperemia in a randomized crossover design during incomplete balloon occlusion (“balloon”) and with the deflated balloon in the right atrium (“sham”). The primary end point of the study is the change in index of microvascular resistances (IMR) after acute modulation of CS pressure, while key secondary end points include changes in the other parameters.

**Discussion:**

The aim of the study is to investigate whether occlusion of the CS is associated with a decrease in IMR. The results will provide mechanistic evidence for the development of a treatment for patients with MVA.

**Clinical trial registration:**

https://clinicaltrials.gov/, identifier NCT05034224.

## Introduction

Microvascular angina pectoris (MVA) is a complex clinical condition in which functional and/or structural changes in the coronary microcirculation result in an increased vascular tone. MVA is diagnosed as symptoms of ischemia with objective evidence of impaired coronary microvascular function [e.g., an index of microvascular resistance (IMR) > 25] in the absence of obstructive epicardial disease (1, 2). While the clinical attention and academic interest in this field is growing, the mechanisms behind its pathophysiology and the therapeutic alternatives available remain incompletely investigated (3). Despite these uncertainties, there is a consensus that this condition is clinically relevant as it affects up to two-thirds of patients who suffer from stable angina and either have no epicardial coronary stenosis at angiography or have combined epicardial and microvascular disease (4).

Microvascular angina caused by a dysfunctional microvascular bed cannot be treated by standard revascularization therapies and the pharmacological strategies (e.g., nitrates, calcium channel blockers, ranolazine) available also provide limited benefit. As well, while pressure-controlled intermittent coronary sinus occlusion has been shown to improve microvascular resistances in the setting of acute myocardial infarction (5), there is little evidence that interventions may improve microvascular resistances in patients with chronic coronary syndromes.

As a possible alternative to pharmacological agents, the hypothesis of improving myocardial perfusion by diverting blood from the coronary venous system to an ischemic region (“venous retroperfusion”) has again gained attention during recent years. This therapy is based on the concept that an elevation in backward pressure in the coronary venous system provokes dilatation of the subendocardial arterioles, resulting in a relative reduction of vascular resistance in this area and a redistribution of blood flow to the ischemic subendocardial layers (6–8). Numerous studies confirm the efficacy of this approach for the therapy of patients who have angina and are not candidates for “traditional” revascularization (6). The study presented here aims to investigate the effect of an increase in coronary sinus pressure on microvascular function, a potentially new therapeutic concept.

## Materials and methods

### Overview

We investigate whether an increase in coronary sinus pressure leads to a change in coronary microvascular resistances in patients with angina pectoris due to microvascular dysfunction.

### Study design

The study is a sham-controlled, crossover, randomized trial to investigate the effect of changes in coronary venous pressure on microvascular resistances. The hypothesis of the study is that occlusion of the coronary sinus (CS) will be associated with a decrease in the index of microvascular resistances (IMR). The protocol complies with good clinical practice and the ethical principles described in the Declaration of Helsinki and has been approved by the local ethics committee. All patients will provide written informed consent before enrollment.

### Study population

Patients must meet all of the following inclusion criteria: chronic coronary syndrome (including patients with anginal equivalents); reversible ischemia on non-invasive testing; absence of epicardial stenosis that are compatible with the symptoms and the evidence of ischemia; evidence of microvascular dysfunction as demonstrated by an IMR ≥ 25; willingness to participate and ability to understand, read, and sign the informed consent; age > 18 years.

Patients will be excluded from eligibility for study enrollment if any of the following criteria applies: previous coronary artery bypass graft (CABG) with patent graft to the left anterior descending coronary (LAD) such that IMR cannot be measured; epicardial coronary disease (FFR < 0.80 with evidence of a focal stenosis) in the LAD territory; second and third degree atrioventricular block; severe valvular heart disease; any cardiomyopathy; pulmonary or renal disease; inability to provide informed consent; any disease reducing life expectancy. Patients unable to understand the scope of the study are classified as not able to give informed consent and are excluded for eligibility for study enrollment. Likewise, patients unable to consent, e.g., for a neurological damage, are treated as not able to give informed consent and are excluded for eligibility for study enrollment (Table 1).

**TABLE 1 T1:** In- and exclusion criteria.

Inclusion criteria (ALL)	Exclusion criteria (ANY)
● Chronic coronary syndrome (including patients with anginal equivalents)	● Previous CABG with patent grafts such that IMR cannot be measured
● Reversible ischemia on non-invasive testing	● Epicardial coronary disease (FFR < 0.80 with evidence of a focal stenosis) in the LAD territory
● Evidence of microvascular disease with IMR = 25	● Second and third degree atrioventricular block
● Willingness to participate and ability to understand, read, and sign the informed consent	● Severe valvular heart disease
● Age>18 years	● Any cardiomyopathy
	● Pulmonary or renal disease
	● Inability to provide informed consent
	● Any disease reducing life expectancy

### Procedures

#### Recruitment

Patients will be enrolled among those treated at the Department of Cardiology, Cardiology I of the University Medical Centre Mainz or, eventually, cooperating centers.

#### Randomization

Microvascular function measurements will be made (both at rest and during hyperemia) twice in each patient in a sham-controlled, randomized, crossover design. Randomization will be performed after informed consent and if all inclusion criteria and no exclusion criteria are met. Patients will be randomized 1:1 to one of the two study arms (sham/balloon or balloon/sham) (Figure 1). After the first set of rest/hyperemia measurements in the first condition (balloon or sham, Figure 1), and a 10 min waiting time, patients will cross-over to the other condition (sham or balloon) and the measurements (rest/hyperemia) will be repeated.

**FIGURE 1 F1:**
[figure not shown]
Randomization.

For the measurements during balloon inflation, incomplete CS occlusion will be achieved with a Swan-Ganz catheter advanced into the CS with access through the femoral or jugular vein. The position of the balloon will be chosen in order to cause a ∼80–90% CS lumen reduction while maintaining stability throughout the measurements. For the sham measurements, the balloon will be kept deflated in the right atrium. Randomization will be done by a computer-generated random sequence (MedCalc, Ostend, Belgium).

#### Hemodynamic measurements

Coronary angiography and microvascular function assessments will be performed in the left anterior descending coronary artery using the wire-based thermodilution method. Five to seven thousand international units of intravenous heparin and intracoronary nitrates will be administered before measurements when systolic blood pressure is above 100 mmHg systolic. A guiding catheter will be advanced to the ostium of the left coronary. A pressure wire (Pressure Wire X; Abbott Vascular, Santa Clara, CA, United States) equipped with pressure sensor and thermistor will be advanced placed approximately 8 cm into the LAD after ostial equalization. Maximal hyperemia will be induced through intravenous adenosine (140 μg⋅kg^–1^⋅min^–1^) or, in patients with asthma, intracoronary papaverine (10 mg). The distal sensor of the pressure wire will be kept in the same position and the same hyperemic agent will be used for the two sets of measurements (sham and balloon). For the assessment of the mean transit time (Tmn) and IMR, 3 boli of 3 ml room-temperature saline will be injected briskly into the guiding catheter as per instructions for use. The presence of drift will be checked at the end of the measurements. All assessments will be performed using the CoroFlow software (Coroventis, Uppsala, Sweden).

### Trial endpoints

The primary analysis will be on the per-protocol principle (i.e., including all patients who are not protocol violators).

Primary endpoint: change in IMR during inflation of the CS balloon as compared to sham.

Key secondary endpoints: changes in the following physiological parameters

1.Aortic (Pa) and distal coronary pressure (Pd) at rest and during hyperemia (aortic and coronary pressure);2.Pressure in the right atrium (Pra) and in the coronary sinus (Pcs);3.RFR (resting flow ratio);4.FFR calculated as Pd/Pa and as (Pd-Pcs)/(Pa-Pcs);5.Tmn (transit mean time) at rest and during hyperemia, average of the three boli;6.CFR: coronary flow reserve;7.IMR calculated as [(*P*_*d*_ – CS) × *T*_*mn*_] and using the standard formula (IMRst = *P*_*d*_ × *T*_*mn*_). CFR is the ratio of baseline *T*_*mn*_/hyperaemic *T*_*mn*_.

### Safety

All measurements (including hemodynamic measurements) are applied as clinically indicated and according to CE certificate and the instruction for use. Vascular access is performed using the femoral or jugular vein; the expansion of the balloon is incomplete and performed using low pressure (2–4 ATM). The risk of trauma is thereby minimal. Thus, it is not to be expected that the participation in the study will lead to unneeded or harmful therapeutic interventions.

### Statistics

Statistical analysis will be performed with MedCalc (Ostend, Belgium).

#### Power calculation

The study is powered for the primary efficacy endpoint IMR. In the OxAMI-PICSO study (5), PICSO reduced the IMR in patients with no reflow after ST-elevation myocardial infarction from 45 [22–51] to 25 [19–36]. In unselected coronary artery disease patients, Mangiacapra et al. (9) reported a decrease in IMR from 27 ± 11 to 19 ± 9 after intracoronary enalaprilat; Suda et al. (10) reported a decrease in IMR from ∼28[21–35] to ∼19[17–23] (*P* < 0.0001, median decrease ∼35%) in response to fasudil. Luo (11) reported baseline IMR of 33 units in patients with microvascular dysfunction (i.e., our expected population), with a baseline SD of 7.6 units. When assuming a baseline IMR of 33 and conservatively using the pooled baseline SD of IMR 13 units of both treatment groups from Mangiacapra, and assuming a similar effect as that observed in the papers by Mangiacapra and Suda, this will result in an effect size of ∼0.69 (∼9/13). With this effect size and a power of 80%, 19 patients are needed. In case of missing data, this sample size could be increased to 25.

#### Statistical analysis

The primary analysis will be done for the IMR measurement. The primary hypothesis is H0: μExp = μSham, vs. H1: μExp ≠μSham, where μExp and μSham are the expected values of the IMR with experimental intervention (balloon) and sham. The primary analysis will be performed as within-subject comparison of the primary parameter. Statistical tests and effect estimates will be calculated using the Wilcoxon test. The effect of randomization and baseline measurements as covariates will be investigated. No treatment by time interaction is expected because the balloon from the experimental intervention will produce a transient increase in CS pressure which will normalize upon deflation. The primary comparison will be performed at a two-sided significance level of α = 0.05. Treatment differences will be displayed by adjusted estimates and 95% confidence intervals. Bias is minimized by randomized sequence allocation. The randomization ratio of the treatment sequences will be 1:1 without any stratification factors. Randomization with permuted blocks will be applied.

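### The Wilcoxon test named for the primary comparison has no period term and cannot give the adjusted estimates the plan promises; one period-adjusted primary analysis should be named

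*Protocol article*

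**What the plan says.** Under Randomization, patients are allocated 1:1 to sham then balloon or balloon then sham, with 10 minutes between conditions. Under Statistical analysis, the hypothesis concerns means, "where μExp and μSham are the expected values of the IMR with experimental intervention (balloon) and sham", and the primary analysis is a within-subject comparison. The article then states: "Statistical tests and effect estimates will be calculated using the Wilcoxon test". On covariates it says: "The effect of randomization and baseline measurements as covariates will be investigated". On reporting it says: "Treatment differences will be displayed by adjusted estimates and 95% confidence intervals". Its only remark on time is: "No treatment by time interaction is expected because the balloon from the experimental intervention will produce a transient increase in CS pressure". The level is 0.05, two-sided, and allocation uses permuted blocks without stratification. Under Trial endpoints, the primary analysis set is per-protocol.

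**The concern.** Three statements in the Statistical analysis section do not fit together. A paired Wilcoxon test accepts no covariates. It can be accompanied by a Hodges–Lehmann estimate and interval, but not by an adjusted one. If the Wilcoxon test supplies the effect estimate, the adjusted estimate must come from a second, unnamed analysis, so the headline figure for the primary endpoint is not fixed.

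The named test also pools balloon-minus-sham differences without regard to order. The argument that coronary sinus pressure normalises after deflation is an argument against carryover. It does not exclude a shift common to all patients between the first and second set of measurements. The Hemodynamic measurements section leaves room for one: nitrates are given before the measurements, hyperaemia is induced twice, and wire drift is checked at the end.

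With equal sequences, a period shift widens the spread of the pooled differences and costs power. With unequal sequences, it also enters the estimate.

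**Working it through.** **Inputs from the article.** Effect 9 IMR units, SD 13, effect size about 0.69, power 80%, N = 19 (Power calculation); 20 patients planned (Abstract); two-sided α = 0.05 (Statistical analysis).

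**Assumptions.** The period shift π is not given, so a range is shown. Following the article's ratio 9/13, the SD of within-patient differences is taken as 13, although the article describes that figure as a baseline SD. Differences are taken as normal.

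**1. The stated sample size.** Paired t test, noncentral t, d = 0.69, df = n − 1: power is 78.8% at n = 18 and 81.2% at n = 19. The stated 19 is reproduced.

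**2. The same with period adjustment.** The estimate is the average of the two sequence means of balloon minus sham, with df = n − 2. Power is 80.9% at n = 19 and 83.1% at n = 20. Adjustment costs 81.2 − 80.9 = 0.3 points and no patients.

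**3. How a shift enters.** Let D be balloon minus sham, δ the treatment effect and π the second-period shift.
- Sham/balloon (n1 patients): mean of D = δ + π.
- Balloon/sham (n2 patients): mean of D = δ − π.
- Unadjusted mean: δ + π(n1 − n2)/N.
- Average of the two sequence means: [(δ + π) + (δ − π)]/2 = δ, with no bias.
- SD of the pooled differences at 10/10: √(13² + π²), which is √178 = 13.3 for π = 3, √194 = 13.9 for π = 5 and √233 = 15.3 for π = 8.

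**4. Power at 10/10, δ = −9 (simulation; runs agree within about two points).**

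| Assumed shift | Pooled signed-rank | Period-adjusted t |
|---|---|---|
| 0 | 81–83% | 83–84% |
| 3 | 80–81% | 83–84% |
| 5 | 77–78% | 84–85% |
| 8 | 70% | 83% |

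The small gap at zero shift comes from using ranks, not from ignoring period. The type I error of the signed-rank test at 10/10 is 4.5% with no shift and 1.7% at a shift of 9, so the test becomes conservative.

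**5. Bias of the unadjusted mean at a shift of 5.**
- 10/10: 0.
- 10/9: 5 × 1/19 = 0.26.
- 11/9: 5 × 2/20 = 0.5.
- 12/8: 5 × 4/20 = 1.0.
- 13/7: 5 × 6/20 = 1.5, so an effect of −9 would be estimated as −7.5.

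**6. Direction when sequences are unequal.** At 11/9 and a shift of 5 against the effect, signed-rank power is 72% against 83% adjusted; with the shift in favour of the effect, both are 82%. At 12/8 the corresponding figures are 67% against 82%, and 86% against 82%. At 13/7, signed-rank type I error rises to 6.2% at a shift of 5 and 7.2% at 9.

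**The case against.** The strongest reply is that the article does not ignore order. Sequence is the only thing randomised, so the covariate sentence most naturally refers to it, and in an analysis of within-patient differences a sequence covariate is the period adjustment. A reader might infer that period is left out altogether; that sentence does not support so strong a reading. What stands is that sequence is merely to be investigated and is not tied to the primary test. The article also says only Wilcoxon, and a rank-sum test on period differences would be a Wilcoxon test that allows for period. The within-subject wording makes the signed-rank reading likelier, and the text does not settle it.

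Second, no period effect is documented, and a shift of 8 would be nearly as large as the assumed treatment effect. The same wire position and hyperaemic agent are required for both sets of measurements. At a shift of 3 the loss is only about three points. This stands: the loss is conditional.

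Third, permuted blocks keep the sequences close to 1:1. Starting from the maximum of 25 patients split 13/12, reaching 13/7 by five random exclusions has probability C(12,5)/C(25,5) = 792/53,130 = 1.5%. This also stands: 13/7 is a stress case.

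Two further inferences are tempting. One is that the signed-rank test is invalid because the hypothesis concerns means. The two targets coincide when the differences are symmetric, and a rank method is defensible with about 20 patients, so this is minor. The other is that baseline covariates would adjust away part of the effect. Under Trial endpoints, baseline transit time does mean the resting value, but under Power calculation baseline IMR is the pre-treatment value, and nowhere are in-condition resting values named as covariates. That reading is speculative.

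Finally, a protocol article may leave model detail to an analysis plan that is not shown. That does not answer the point, because this article itself fixes the test and promises an estimate that the test cannot give.

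**Conclusion.** The point holds in a limited form. The mismatch between the named test and the promised adjusted estimates is in the text and needs no assumption. That the remark on time does not cover a period main effect is likewise plain from the wording.

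The numerical harm is conditional on a period effect of unknown size, normal differences and an SD of 13. At 10/10 the loss against an adjusted analysis is about 3 points at a shift of 3, 7 at a shift of 5 and 13 at a shift of 8. Near-balanced sequences give little bias, at most 10% of the shift up to 11/9. Beyond balance, power and type I error can move either way, so it would be wrong to say that the test always loses power or is always conservative.

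A reader might infer that the trial is underpowered or its estimate biased as planned. The documents do not support that: with no period effect there is no bias, and 19 patients are enough with or without adjustment. The case for change is that it protects against a plausible effect at almost no cost and settles which estimate is primary.

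**What to change.** Name one period-adjusted primary analysis before the data are analysed. Either of these would do:

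- a linear or mixed model of IMR with treatment, period and sequence and a random patient effect, equivalently a two-sample comparison of period differences between sequences; or
- its rank version, a rank-sum test on period differences with a Hodges–Lehmann estimate and confidence interval.

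Report that adjusted difference with its 95% CI as the primary result, and keep the signed-rank test as a sensitivity analysis. If a baseline covariate is used, restrict it to a value measured before the first condition.

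The change needs new analysis wording and no new data. The linear form costs one degree of freedom, and N = 19 gives 80.9% power on the article's inputs. The rank version is slightly less powerful under normal differences, at about 79–80% for 10/10 and 77–78% for 10/9, and hardly varies with the shift. That should be weighed if a rank method is preferred because IMR is skewed.

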### Data management

Patient data will be pseudonymized and collected by the study team. Pseudonymized patient data will be stored digitally on an external hard-drive not connected to the clinical intranet and only accessible to the members of the study team. After 10 years of storage, data will be destroyed. It is not intended to give study participants’ data to a third party. All data will be analyzed after the last patient is discharged from index hospitalization. No interim analysis is intended. However, a Data Safety Monitoring Board consisting of two physicians not affiliated with the study will monitor the safety of the subjects throughout the study. In case a study participant withdraws consent after having his data collected from him, the patient’s data will be anonymized.

### Ethics and publication policy

The protocol has been approved by the local state medical association’s ethics committee. In accordance with the WMA Declaration of Helsinki–Ethical Principles for Medical Research Involving Human Subjects, researchers, authors, sponsors, editors, and publishers all have ethical obligations with regard to the publication and dissemination of the results of research. Researchers have a duty to make publicly available the results of their research on human subjects and are accountable for the completeness and accuracy of their reports. All parties should adhere to accepted guidelines for ethical reporting. Negative and inconclusive as well as positive results must be published or otherwise made publicly available. Sources of funding, institutional affiliations and conflicts of interest must be declared in the publication. Reports of research not in accordance with the principles of this Declaration should not be accepted for publication. The PI of this study, recognizing the seminal importance of this investigation, is committed to the unrestricted and widespread dissemination of all primary and secondary endpoint results and tertiary analyses. At the conclusion of the study, an abstract reporting the primary results will be prepared by the Principal Investigators and presented at an annual scientific meeting. A publication will similarly be prepared for publication in a reputable scientific journal. Following analysis and presentation of the primary endpoint results, active participation of all study group members will be solicited for data analysis and abstract and manuscript preparation and therefore included as co-authors. Submission of all abstracts and publications regarding the primary endpoint and secondary endpoints from the study requires approval by the Principal Investigators after review by all members of the study group.

